### 2.8. Validation in Cell Lines

In vitro studies will be conducted to validate the in silico predictions, using biochemical and immunohistochemical assays to quantify glucose and glycogen levels in neuronal and HEK293 cell lines (see Figure 2).

## 3. Procedure

### 3.1. Recruitment

Informed written consent will be obtained from all patients or their legal representatives before inclusion in the study, in line with institutional and national ethical guidelines. Participant will be made aware that their involvement is voluntary and that they can withdraw from the study at any time.

### 3.2. Intervention Description

The drug that we chose to use is empagliflozin. The potential benefit of gliflozins in LD is supported by the following evidence [19,29,35,36,37,38,39]: (1) a relationship is established between altered brain metabolism and the onset of epileptic seizures; (2) the SGLT2 protein is expressed in the brain and its inhibition may reduce both glucose and sodium loads, which may decrease neuronal excitability; (3) gliflozins produce metabolic effects similar to those of the ketogenic diet; (4) ongoing clinical studies are testing empagliflozin in the treatment of epilepsy (https://clinicaltrials.gov/, accessed on 3 May 2025); (5) the neuroprotective effects of gliflozins have been reported in animal models of Alzheimer’s disease and stroke; (6) gliflozins inhibit glycogen accumulation in the kidney in mouse models of glycogen storage disease type 1b and type XI; (7) gliflozins ameliorate phenotypes in LD zebrafish models.

The pharmacokinetic profile of empagliflozin is well documented and has been specifically described in the context of young patients [40,41,42].

Empagliflozin will be orally administered once daily at a dose of 10 mg for 6 months in two patients with LD in the initial or intermediate stage (10–22 years). The proposed treatment duration is based on the pilot nature of the study, as well as on the previous use of empagliflozin in studies involving the treatment of other rare glycogen storage diseases, such as GSD type 1 [23,43].

The goal is to assess its efficacy and tolerability during the presumed phases of initial degeneration and LB accumulation, with the aim of slowing down disease progression.

### 3.3. Participant Timeline

The overall duration of the project is 16 months, with a screening period (4 months), an open-label treatment phase (6 months), and a follow-up period (6 months). Patients will undergo a clinical evaluation at baseline (week 1, before the administration of empagliflozin 10 mg/day), at the intermediate time point (three months), and at the end of treatment (six months). Sub-analyses will also compare seizure rates at intermediate time points. The progression of other LD symptoms will be evaluated at 6 months and compared to the baseline. Changes in FDG-PET and MRI findings will be categorized as stable, improved, or worsened.

### 3.4. Outcomes

The measurement, at 3 and 6 months, of safety and clinical outcomes will be compared qualitatively with prognosis data available in the literature.

The following parameters will be determined: vital signs; weight and height; general and neurological examination; seizure diary; adverse event assessment; ECG; urine and serum pregnancy tests; laboratory tests (hematology, chemistry, and urinalysis); video-EEG/polygraphy; and high-field brain MRI (3 Tesla) and brain PET with ^18^F-fluorodeoxyglucose (at baseline and 6 and 12 months of treatment). Neuropsychological assessments will include the Montreal Cognitive Assessment (MoCA), Leiter Performance Scale 3, Visual Motor Integration test, children’s color trail test, NEPSY-II inhibition subtest, phonemic and semantic verbal fluency test, and Weiss working memory and vocabulary subtests. Motor function assessments will include the 4-stage balance test, timed up and go, 6 min walk test, 10 m walk test, 9-hole peg test, Scale for the Assessment of Ataxia (SARA), and Scale for the Assessment of Myoclonus (UMRS). Assessments of global function and autonomy will include the Lafora Disease Performance Scale (LDS), Lafora Epilepsy Severity Scale (LESS), Activities of Daily Living (ADL) and Instrumental Activities of Daily Living (IADL) scales, Barthel Index, Vineland-II Adaptive Behavior Scales, and Clinical Global Impression scales (CGI-I and PGI-CaGI-C). All assessments will be performed by the same investigator and video-recorded (with informed consent).

The following endpoints for the safety and efficacy of empagliflozin will be evaluated from baseline to month 6:Safety: Type, severity, incidence, and timing of adverse events; incidence of treatment discontinuation due to adverse events; and changes in vital signs, ECG, and laboratory parameters.Efficacy: Change in the frequency of generalized tonic–clonic seizures compared to the 6 months prior to the study; EEG: changes in posterior background activity and frequency of epileptiform abnormalities; cognitive function: changes (no worsening or improvement) in neuropsychological assessments; motor function: changes (no worsening or improvement) in motor function assessments; global function and autonomy: changes (no worsening or improvement) in LDS, LESS, ADL, IADL, Barthel Index, Vineland-II, and CGI-I and PGI-CaGI-C scales.Biomarkers: Brain FDG-PET: changes (no worsening) in areas of cerebral hypometabolism. High-field brain MRI (3 Tesla): changes (no worsening) in measures of cerebral atrophy. Direct measurement of CSF polyglucosan levels, although potentially informative, is not feasible within the constraints of this pilot study. Thus, brain FDG-PET imaging is included as a surrogate biomarker to assess changes in cerebral metabolism. This choice was primarily due to the significant logistical challenges associated with sample collection and processing for this ultra-rare disease, as well as to the absence of widely available, fully validated assays for the quantitative analysis of CSF polyglucosan levels.

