### 2.2. Eligibility Criteria

A single-center, observational, controlled pilot study will be conducted at the Neurology Unit of IRCCS Casa Sollievo della Sofferenza Hospital in San Giovanni Rotondo (Foggia, Italy). The stage of disease progression will be assessed using a disability scale that considers cognitive and motor functions, activities of daily living, and social interaction [32,33]. The stages are defined as follows: 1—mild cognitive and motor deterioration: preserved activities of daily living and social interaction; 2—moderate cognitive deterioration: limitations in motor activities and social interactions; 3—severe cognitive and motor deterioration: need for assistance with walking and activities of daily living and poor social interaction; 4—wheelchair-bound or bedridden patients: no significant activities of daily living and social interaction. Patients will be enrolled based on the following criteria:

Inclusion Criteria:
Documented genetic diagnosis of LD (pathogenic mutations in the EPM2A or EPM2B genes);Age: 10–22 years;Early–intermediate stage of disease (1–2 progression scale) [32,33];Patient able to understand and complete the protocol (even with the help of a caregiver over 18 years of age) and perform neuropsychological tests.

Exclusion Criteria:
Undocumented genetic diagnosis of LD;Advanced stage of disease (3–4 progression scale) [32];Participation in other ongoing therapeutic treatments for LD;Pregnancy;Allergy or known hypersensitivity to empagliflozin;Other conditions, at the discretion of the investigator, that could interfere with participation or completion of the study.

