### 2.4. Sample Size

This pilot study aims to evaluate the safety and efficacy of empagliflozin initially in two patients with genetically diagnosed LD in the early/intermediate stage of disease. The sample size of two patients was chosen based on the feasibility of recruiting patients with these specific characteristics and the exploratory nature of this pilot study.

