## 4. Expected Results

Many of the therapeutic strategies proposed for the treatment of LD are still under investigation or have shown partial efficacy in patients, failing to halt disease progression. The expected outcomes of this study are to assess the safety and tolerability of empagliflozin in patients with LD and to gather preliminary data on its potential efficacy in improving clinical and neurologic outcomes. We recognize that the lack of a control or comparison group in the proposed single-arm observational design is a limitation. However, to mitigate the absence of a concurrent control group, we will conduct a comparative analysis using data from natural history studies, such as those evaluating metformin or VAL-1221 [9,49]. This approach will allow us to assess potential deviations from the expected disease trajectory and provide a more nuanced interpretation of the observed outcomes. Additionally, the in silico and in vitro studies, complementary and conducted in parallel with the in vivo human study, are expected to provide insights into the mechanisms through which empagliflozin may exert its therapeutic effects in LD. These findings will be important for guiding and supporting future research and development efforts aimed at repurposing empagliflozin or similar drugs for LD. By repurposing an already-approved drug, this research may significantly shorten the time and reduce the costs associated with developing a new therapy for LD patients. This has particular importance considering the rapid progression of the disease and the urgent need for effective treatment options.

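### A qualitative comparison of two patients with published prognosis cannot separate a deviation from the expected course from ordinary between-patient variation

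*Protocol article*

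**What the plan says.** Section 2.4 fixes the size of the study: "The sample size of two patients was chosen based on the feasibility of recruiting patients with these specific characteristics". Section 2.6 plans descriptive summaries and changes from baseline, with no threshold or decision rule.

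Section 3.4 sets the method of the external comparison: "The measurement, at 3 and 6 months, of safety and clinical outcomes will be compared qualitatively with prognosis data available in the literature". It also says that the "endpoints for the safety and efficacy of empagliflozin will be evaluated from baseline to month 6". For most efficacy outcomes it gives a direction but no size, for example "cognitive function: changes (no worsening or improvement) in neuropsychological assessments".

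Section 4 concedes that "the lack of a control or comparison group in the proposed single-arm observational design is a limitation". As mitigation it offers the following: "we will conduct a comparative analysis using data from natural history studies, such as those evaluating metformin or VAL-1221". It then says what this will achieve: "This approach will allow us to assess potential deviations from the expected disease trajectory". The same section makes supportive results the starting point for larger controlled trials.

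No section gives a reference rate of decline, the spread of decline between untreated patients, a plan to match the reference patients on stage, or a criterion for calling a course better than expected.

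**The concern.** The article does not leave the method open. It chooses a qualitative comparison and gives it an inferential task, which is to show whether a treated patient has left the expected course. One patient's course can be judged unusual only against the variation among untreated patients. A reading against a typical or described course has no such reference, so a patient who happens to decline slowly looks like a patient who responded.

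This is separate from the choice of comparator studies. The examples named in section 4 are studies that evaluate treatments, which raises its own question. The present point would remain with a perfectly matched untreated cohort.

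At stake is how the pilot will be read. Treatment is open-label (section 3.3) and one investigator performs all assessments (section 3.4), so a qualitative judgement has room to lean favourably. Ordinary variation in two patients could then be presented as preliminary evidence of efficacy and carried into the case for the next trial.

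**Working it through.** **Figure in the plan.** There is none to reproduce. The article states no alpha, power or false-favourable rate, and two patients were chosen for feasibility.

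**Inputs**
- Number of patients: 2 (section 2.4).
- Type of comparison: qualitative, against published prognosis (section 3.4).
- Drug effect: none (assumption, to see what chance alone produces).
- Share p of comparable untreated patients who do better than the yardstick: not in the documents. It is 0.5 if the yardstick is the median course, or the mean of a symmetric distribution. I vary it from 0.3 to 0.7.
- The two patients are independent (assumption, relaxed below).

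**Formulas**
- Both look favourable: p².
- At least one looks favourable: 1 − (1 − p)².

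| p | both | at least one |
|---|---|---|
| 0.3 | 0.09 | 0.51 |
| 0.4 | 0.16 | 0.64 |
| 0.5 | 0.25 | 0.75 |
| 0.6 | 0.36 | 0.84 |
| 0.7 | 0.49 | 0.91 |

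**Sensitivity to the assumptions**
- *Skewed decline.* If decline is lognormal and the published mean is the yardstick, p = Φ(σ/2). For σ = 0.5, p = 0.60 and p² = 0.36. For σ = 1.0, p = 0.69 and p² = 0.48.
- *Correlated patients.* At p = 0.5, P(both) = 1/4 + arcsin(ρ)/(2π). This is 0.28 for ρ = 0.2 and 0.33 for ρ = 0.5.
- *Several domains.* At p = 0.5, with k independent domains, the chance that at least one domain favours both patients is 1 − 0.75^k: 0.44 for k = 2 and 0.68 for k = 4. Real domains are correlated, so these two values overstate the effect.

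**What a spread-based rule changes.** With a two-sided 95% prediction interval, an untreated patient falls outside on the favourable side with probability 0.025. For one outcome:
- both patients: 0.025² = 0.0006
- at least one of the two: 1 − 0.975² = 0.049

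Under the illustrative reading at p = 0.5 the corresponding values are 0.25 and 0.75.

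**The case against.** The strongest objection is that the yardstick in these calculations is not the protocol's. Neither section 3.4 nor section 4 mentions a mean, a median or a typical course, and published prognosis data may include ranges. No rule requires both patients to look favourable, and the planned statistics are descriptive. Section 4 speaks of assessing possible deviations and does not claim any. This stands: a reader might take 25% as the study's false-positive rate, and the documents do not support that. Nor do they support assuming that patients would be judged against a confidence interval around a published mean; the only confidence intervals planned (section 2.6) summarise the study's own data.

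The stated favourable direction also differs in part. Not worsening from baseline is a different bar from declining less than a typical patient, and the coin-toss figure does not describe it.

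Two further inferences fail:
- A reader might conclude that the literature is the study's only substitute for a control. It is not: section 3.4 compares tonic–clonic seizure frequency with each patient's own preceding six months. That comparator is weak but real.
- Section 2.2 says "The stage of disease progression will be assessed using a disability scale", and section 3.4 does not list that stage among the follow-up measures. A reader might infer that nothing followed can be set against published work. But section 3.4 follows LDS, LESS, SARA, UMRS and other named scales, so re-scoring the stage is not needed on that ground.

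It can also be said that reference intervals belong in an analysis plan, that stage-matched untreated data may be scarce in a disease with about 300 estimated cases worldwide, and that the article openly calls the study exploratory and concedes the missing control. Scarcity is a fair warning, and the fix allows for it. The other two do not remove the point, because the article itself names the method and presents it as the remedy for the missing control.

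**Conclusion.** The concern holds in a limited form. Section 3.4 fixes a qualitative comparison of two individuals with the literature, and section 4 says that a literature comparison will let the investigators assess deviations from the expected course. Without reference to the spread between untreated patients, the stated method cannot do that, however good the comparator.

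The size is an illustration and not an operating characteristic of the plan. For an inert drug, two independent patients and a typical untreated course as yardstick, both patients look favourable about 25% of the time. The range is about 9% to 49% for an assumed share p of 0.3 to 0.7. Right-skewed decline judged against a mean, or positive correlation between the two patients, pushes the figure above 25%. If the reference patients were treated, p could move either way.

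**What to change.** In section 3.4, replace the qualitative comparison with a stated rule:

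1. For each outcome already collected for which published untreated data give a spread, report each patient's month-6 change as a percentile of untreated patients at a comparable stage, or against a 95% prediction interval from them.
2. Use the words *better than expected* only when the patient lies outside that interval on the favourable side. Otherwise write *within the range of untreated disease*.
3. Where no source gives a spread, remove the statement about deviations in section 4 for that outcome and describe the patient's course.

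Report every outcome handled under rule 1, so that a single favourable one is read against the number examined.

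The cost is a search for usable untreated data and some rewording; no patients, visits or measurements are added. The downside is that most results will read as within the expected range, and for some outcomes the claim will have to go.

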### 2.5. Data Collection and Management

Data will be entered into an electronic database. The following baseline data will be collected: informed consent; inclusion/exclusion criteria; demographic data; comprehensive medical and neurological history; detailed history of epileptic seizures, including frequency of generalized tonic–clonic seizures in the last six months (based on previous clinical documentation and/or a seizure diary); and medication history.

All information of the study protocol and the results obtained will be collected by the investigator during the study period and stored at IRCCS Casa Sollievo della Sofferenza Hospital in San Giovanni Rotondo (Foggia, Italy).

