### 2.6. Statistical Methods

Descriptive statistics will be used to summarize the data. For continuous variables, measures such as mean, standard deviation, minimum, maximum, and 95% confidence intervals will be calculated. For categorical variables, the frequency and percentage will be reported. Changes from the baseline to follow-up time points will be assessed.

The in silico and in vitro studies proposed here are complementary and will be conducted in parallel with the in vivo human study. The aim of these studies is to gain insight into the additional mechanisms of action of empagliflozin that may be relevant for LD.

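### The 95% CI planned for continuous variables would, for the seizure endpoint, be taken across two patients and would not reflect the uncertainty in either patient's own seizure counts

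*Protocol article*

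**What the plan says.** The Abstract makes change in the severity of epilepsy a primary endpoint. Section 3.4 (Outcomes) lists as its first efficacy measure "Change in the frequency of generalized tonic–clonic seizures compared to the 6 months prior to the study", within a set introduced by "The following endpoints for the safety and efficacy of empagliflozin will be evaluated from baseline to month 6". Section 2.5 gives the source of the baseline figure: "frequency of generalized tonic–clonic seizures in the last six months (based on previous clinical documentation and/or a seizure diary").

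On analysis, section 2.6 says: "For continuous variables, measures such as mean, standard deviation, minimum, maximum, and 95% confidence intervals will be calculated". It adds that changes from baseline will be assessed. Section 2.4 fixes the sample: "The sample size of two patients was chosen based on the feasibility of recruiting patients with these specific characteristics". Section 3.3 adds shorter comparisons: "Sub-analyses will also compare seizure rates at intermediate time points".

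The outside comparison in section 3.4 is one in which outcomes are "compared qualitatively with prognosis data available in the literature". Section 4 also plans a comparison with natural-history data, without naming a method. No responder threshold is set, and no section speaks of chance variation in one patient's seizure counts.

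**The concern.** Seizure frequency here is a count within one person over two windows of about six months. The information about its precision lies in the number of events in each window. A mean, SD and CI of two changes use only how far the two patients differ from each other. Such an interval can be very narrow when the counts say little, and very wide when they say something. Listing the two changes without intervals would leave the same gap.

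The article proposes to use supportive results as groundwork for larger trials (section 4). At low counts a fall within counting noise could then be read as an early sign of efficacy. The section 3.3 comparisons are more exposed, because shorter windows hold fewer events.

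**Working it through.** The plan has no powered figure to reproduce: the sample size rests on feasibility alone.

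**Inputs from the article.** Two patients (2.4); a six-month baseline window (2.5, 3.4); a six-month treatment window (3.4); mean, SD and 95% CI for continuous variables (2.6).

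**Assumptions not in the article.** Expected generalized tonic–clonic seizures per window, 4 to 20; variance of one patient's count, 1 to 3 times its mean; halving as a yardstick; the same expected count in both windows when the drug does nothing.

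**Step 1: the across-patient interval.** For n = 2 the 95% CI is mean ± t × SD/√2, with t = 12.706 on 1 degree of freedom, so the half-width is 8.98 × SD.

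- Both patients go 6 → 3: changes -3 and -3, SD 0, CI -3 to -3.
- One goes 6 → 0, the other 12 → 3: changes -6 and -9, mean -7.5, SD 3/√2 = 2.12, half-width 8.98 × 2.12 = 19.1, CI -26.6 to 11.6.

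**Step 2: each patient's own interval.** With x seizures before and y on drug in equal windows, y given x + y is binomial with probability p = RR/(1 + RR). The Clopper-Pearson limits for p convert to the rate ratio by RR = p/(1 - p). For 6 → 3, y = 3 of 9, p runs from 0.0749 to 0.7007, and RR from 0.0749/0.9251 = 0.08 to 0.7007/0.2993 = 2.34.

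| Before → on drug | Rate ratio | Exact 95% CI |
|---|---|---|
| 6 → 3 | 0.50 | 0.08 to 2.34 |
| 12 → 6 | 0.50 | 0.15 to 1.44 |
| 6 → 1 | 0.17 | 0.004 to 1.37 |
| 6 → 0 | 0 | 0 to 0.85 |
| 12 → 3 | 0.25 | 0.05 to 0.93 |

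The first example in step 1 looks exact although neither patient's counts exclude no change. The second looks uninformative although, under Poisson counts, both patients' intervals lie below 1.

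**Step 3: chance halving with no drug effect.** X and Y are independent with the same mean. The figure is P(Y ≤ X/2 given X > 0), summed over Poisson or negative binomial probabilities.

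| Expected per window | Poisson | Variance 3 × mean |
|---|---|---|
| 4 | 22% | 38% |
| 6 | 16% | 30% |
| 12 | 6% | 19% |
| 20 | 2% | 12% |

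At 6 expected, at least one of two patients halves with probability 1 - (1 - 0.156)² = 29% (Poisson) to 1 - (1 - 0.3005)² = 51% (variance 3 × mean).

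**Step 4: a rising untreated rate.** Section 1 says that epilepsy becomes refractory as the disease progresses. If the untreated expectation rises from an assumed 6 to 8, the same sum gives 5% (Poisson) to 18% (variance 3 × mean).

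**Step 5: whether the exact interval can serve as a decision rule.** With no drug effect, it excludes 1, in either direction, in 2.4% of patients at mean 6 under Poisson. With variance 3 × mean it does so in 17% at mean 6 and 20% at mean 12; by symmetry, half of these are in the favourable direction.

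**The case against.** The strongest reply is that this is a declared exploratory pilot, described in a condensed article. Section 2.6 never mentions seizures and introduces its list with the words for examples, so the across-patient interval is inferred. Estimator detail is often left to an analysis plan. The article admits that it has no controls, plans outside comparisons and defers efficacy to larger trials.

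Part of this stands. The across-patient reading is the natural one, since each patient yields one change, but it is not spelled out. The point is therefore that the one summary the article states suits this endpoint badly, not that detail is missing. The outside comparisons do not fill the gap: one is qualitative and the other has no stated method.

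The objections to the size of the risk also stand. The expected counts, the halving yardstick, the overdispersion and the flat untreated rate are all assumptions. A reader might infer that 16% to 30% of untreated patients would be declared responders. The article does not support that: it sets no responder rule and gives no seizure counts, and the upper end needs variance three times the mean.

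A reader might also infer that the exact interval should decide whether a patient has changed. Step 5 of the working shows why not: under the overdispersion assumed for the upper figures, it would often certify noise.

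**Conclusion.** The point holds in limited form. On the natural reading of section 2.6, the interval for seizure change is taken across two patients and does not track the evidence in either patient's counts. The 6 → 3 and 6 → 0 / 12 → 3 examples show this in both directions without any assumed seizure rate.

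How often chance alone would produce a halving depends on counts that the article does not give. It is common at 4 to 6 expected seizures per window and uncommon at 20, and rarer still if the untreated rate rises. A reader might infer that the study will report a false benefit; the documents show only that the planned summary gives no protection against one. This is worth correcting because the remedy is cheap, and it calls for no change in sample size or design.

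**What to change.** For the generalized tonic–clonic seizure endpoint and the intermediate-time-point comparisons, replace the across-patient mean, SD and CI with, for each patient:

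- the counts and the days observed in each window;
- the rate ratio (on drug versus the prior six months, or the corresponding shorter windows) with an exact conditional 95% CI that allows for unequal days, labelled as a minimum width because it assumes Poisson counts;
- where dated seizure records exist for both windows, a second interval widened for overdispersion.

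State that a fall whose interval includes 1 will not be read as preliminary evidence of efficacy. Do not adopt exclusion of 1 as a rule for declaring change.

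The main analysis costs a few lines on data already to be collected. The widened interval may not be possible for the baseline, because section 2.5 allows that count to come from clinical documentation without a diary. The downside is that falls from low counts will be reported as inconclusive: from a baseline of 6 in equal windows, only a fall to 0 gives an interval below 1. The intervals cover counting variation only, not regression to the mean or differences in how seizures were recorded before and during the study.

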## 2. Experimental Design

### 2.1. Study Design and Setting

**Objective 1:** The first objective is to evaluate the safety and tolerability of empagliflozin in patients with genetically diagnosed LD in the early to intermediate stages over a 6-month treatment period. Efficacy will be assessed by monitoring changes in the frequency and intensity of epileptic seizures; variations in the background activity and frequency of epileptiform abnormalities on an electroencephalogram (EEG); stabilization of cognitive, behavioral, and motor outcomes, as well as neuro-radiological and metabolic biomarkers (including high-field brain MRI—3 Tesla, brain PET with ^18^F-fluorodeoxyglucose—FDG).

**Objective 2:** The second objective is to investigate the effect of empagliflozin (and SGLT2 inhibitors in general) on targets involved in glucose metabolism and the pathogenesis of LD, aiming to uncover new mechanisms of action and to further support the repurposing of gliflozins in the treatment of LD. Specifically, considering the dysfunctional cellular pathways related to the formation of LBs, two brain glucose transporters (GLUT1 and GLUT3) and glycogen synthase (hGYS) will be explored [30,31]. The interaction with these targets will be evaluated through molecular docking studies, while the ability of gliflozins to reduce intracellular concentrations of glucose and glycogen will be evaluated through in vitro studies using various cell lines.

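### A month-6 FDG-PET change could be a direct effect of empagliflozin on glucose handling, and the plan cannot separate this from a change in disease

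*Protocol article*

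**What the plan says.** All references are to the protocol article.

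- **Role of PET (3.4).** Direct CSF measurement is ruled out as not feasible, and PET takes its place: "Thus, brain FDG-PET imaging is included as a surrogate biomarker to assess changes in cerebral metabolism".
- **Endpoint (3.4).** The biomarker item reads "Brain FDG-PET: changes (no worsening) in areas of cerebral hypometabolism". It belongs to a list introduced by "The following endpoints for the safety and efficacy of empagliflozin will be evaluated from baseline to month 6".
- **Scoring (3.3).** "Changes in FDG-PET and MRI findings will be categorized as stable, improved, or worsened".
- **Dosing (3.2).** "Empagliflozin will be orally administered once daily at a dose of 10 mg for 6 months". Section 3.3 places the baseline evaluation before the first dose and the six-month evaluation at the end of treatment.
- **Scan times (3.4).** MRI and PET are planned "at baseline and 6 and 12 months of treatment".
- **Candidate mechanisms (2.1, Objective 2).** "two brain glucose transporters (GLUT1 and GLUT3) and glycogen synthase (hGYS) will be explored"; and "the ability of gliflozins to reduce intracellular concentrations of glucose and glycogen will be evaluated" in cell lines.
- **Rationale (1 and 3.2).** Gliflozins increase urinary glucose excretion. SGLT2 is present in the brain, and blocking it might lower the glucose load there. The class has metabolic effects resembling those of a ketogenic diet.
- **Design (2.4, 3.3 and 4).** Two patients, open-label treatment, and a single arm, with the missing control group acknowledged as a limitation.

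**The concern.** The PET endpoint is worded as a disease readout: less or no further hypometabolism is favourable, and more is unfavourable. The tracer is a glucose analogue, and the drug under test was chosen because it changes glucose handling. A shift in uptake between a pre-drug scan and an end-of-dosing scan may therefore be pharmacology, disease or both. That FDG uptake depends on glucose transport and blood glucose is general background and is not stated in the article.

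The error could go either way. A drug that lowers glucose entry into brain cells, as Objective 2 will explore, might be labelled as worsening. A shift in the opposite direction, for example through lower blood glucose, might be labelled as improvement. Section 4 names longitudinal PET as a possible surrogate endpoint for later trials, so a mislabelled result could carry forward.

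**Working it through.** The article gives no PET threshold, effect size or variability, so there is no figure to reproduce. The check is whether the design can separate the two explanations.

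1. **What is observed.** For one patient, let D be the change in uptake due to disease from baseline to month 6, and P the direct effect of the drug on uptake at the month-6 scan. The baseline scan precedes dosing, so the drug effect there is zero. Then

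   month 6 − baseline = D + P.

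   This is one equation in two unknowns.

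2. **Two patients.** With separate values there are two equations and four unknowns. If both patients shared the same D and the same P, the second patient would only repeat the sum D + P. Adding treated patients would not help either, since every one of them contributes the same sum.

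3. **External comparison.** Sections 3.4 and 4 plan a comparison with published prognosis and natural-history data. Let E be the disease change expected without empagliflozin. Subtracting it gives (D − E) + P. The external patients carry no empagliflozin effect, so P remains in full.

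4. **Reference-region normalisation.** Suppose the drug multiplies uptake by a factor k in every region. The ratio of a region to a reference region is then (k × region) / (k × reference), and k cancels. If the factor differs by region, the ratio changes by k(region) / k(reference). Normalising removes the uniform part of P and leaves the regional part. The article does not state how the scans are read, so it is unknown whether even the uniform part would be removed.

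5. **The month-12 scan.** Section 3.3 has six months of treatment and six of follow-up, and 6 + 6 = 12, so this scan would fall at the end of follow-up. Section 3.4 labels it as a treatment time point, while Section 3.2 limits treatment to six months. If the scan is off drug and no drug effect persists, month 12 − baseline contains disease change only, but over twelve months. If it is on drug, P is still present. Either way it lies outside the baseline-to-month-6 window.

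The result does not depend on how large P is: at month 6, D and P cannot be separated under this design.

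**The case against.** **The mechanism is not established.** Objective 2 explores GLUT1 and GLUT3, and docking is to find out whether the drug can interact with them at all. This stands. A reader might infer that the protocol says empagliflozin acts on these transporters, so that the PET result will be biased in a known direction. The documents do not support that. They support only that an effect is possible, partly through the systemic and SGLT2 routes in the rationale.

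**The endpoint is regional.** A spatially uniform drug effect could cancel in a relative reading. This also stands, but no such reading is stated, and an uneven effect would remain.

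**PET is a minor endpoint.** The Abstract makes epilepsy severity and cognition primary, and motor function, global function and autonomy secondary. PET is listed under biomarkers, the analysis is descriptive, and no decision rule uses the label. This limits the weight of the point. A reader might also infer that the article treats PET as a measure of polyglucosan burden. It does not: PET replaces an infeasible assay, but its stated purpose is to follow cerebral metabolism. Even so, Objective 1 counts metabolic biomarkers among the means of assessing efficacy, and the endpoint is scored by absence of worsening.

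**Imaging details may sit elsewhere.** Reader masking, glucose at injection and quantification are commonly left to a full protocol or imaging manual. Their absence from an article is not an error and is not claimed as one. They appear below only as remedies. Likewise, the three-way label need not replace numerical results, since Section 2.6 plans summaries of continuous variables.

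**Conclusion.** The concern holds in a limited form. The plan labels a before-drug to end-of-dosing change in FDG uptake as stable, improved or worsened, while its rationale gives reasons why the drug might change uptake directly. A drug effect could be scored as a change in disease, in either direction.

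No size can be given. The documents contain no figure for a drug effect on uptake and no reading threshold, so a statement that both patients would be labelled worsened has no basis. The conclusion assumes that FDG uptake responds to glucose transport or blood glucose, and that the month-6 scan falls while the drug is still acting. The article puts that scan at the end of treatment without giving its timing relative to the last dose.

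Because PET is a descriptive biomarker in two patients, this does not undermine the primary endpoints. It does limit what the trial may conclude from PET, and the wording should be changed.

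**What to change.** In Sections 3.3 and 3.4:

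1. State that the month-6 PET change is a pharmacodynamic (on-drug) measure and will not by itself support a statement that disease has stabilised or worsened. Rest such statements on MRI atrophy and the clinical scales.
2. Record blood glucose at each tracer injection. With three planned scans in two patients, this is 3 × 2 = 6 values. They document one route of drug effect but do not remove the others.
3. Report regional uptake relative to a named reference region, as numbers per patient and scan, beside the three-way label.
4. Have the existing reader assign the label with scan dates hidden and each patient's scans in random order. Treatment is open-label and one investigator performs all assessments, so the label is otherwise open to expectation.
5. Reconcile Sections 3.2, 3.3 and 3.4 on whether the month-12 scan is on or off treatment. If it proves to be off drug, report its difference from baseline as supportive, not as a replacement endpoint, because it covers six further months.

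The cost is a weaker PET claim at month 6 and reading in batches. No new scan, patient or reader is needed.
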